### Study outcomes assessments

2.7

#### Glucose homeostasis outcomes

2.7.1

At each visit, glucose, insulin, and C-peptide will be measured on fresh blood samples drawn after a 12-h fast, as well as 15, 30, 60, and 90, 120 min after the ingestion of 75 g of glucose. Glucose will be measured enzymatically by the hexokinase method whereas insulin and C-peptide will be measured with an electrochemiluminescence immunoassay. The obtained data will be used to calculate the incremental area under the curve for glucose (iAUC glucose) using the trapezoid method from 0 to 120 min. The following indexes will also be calculated: HOMA-IS [Fasting insulin (μU/ml) × fasting glucose (mmol/L)/22.5] (39); Matsuda index {10,000/[fasting glucose × fasting insulin × (mean glucose × mean insulin)]^1/2^} (40); Insulinogenic index [(insulin at 30 min − fasting insulin)/(glucose at 30 min fasting glucose)] (41). The disposition index, which serves as an integrated measure that reflects beta-cell function, will be calculated using Matsuda index × insulinogenic index (41). GDM incidence will be recorded throughout the study based on OGTTs performed during the research visits or based on medical records if not diagnosed during research visits detailed (2).

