**Secondary outcomes:**

Changes in 2-h plasma glucose following the ingestion of 75 g of glucose from the first to the third trimester:

⚬ Glycemic response using the incremental area under the curve for glucose during the 2-h oral glucose tolerance test (OGTT).⚬ Homeostatic Model Assessment for Insulin Sensitivity (HOMA-IS) index, which estimates the hepatic insulin sensitivity (39).⚬ Matsuda index which estimates overall insulin sensitivity (hepatic and peripheral) (40).⚬ Disposition index, which estimates beta-cell function, using Matsuda index*insulinogenic index (41).

Changes in FPG and other indices listed above from the first to the second trimester.

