#### Statistical analyses

2.10.2

The primary analyses will follow the complete case intention-to-treat principle. Changes from first- to third-trimester measurements of the primary and secondary outcomes between the intervention and control groups will be assessed using a two-sample one-sided *t*-test for means. To determine whether the results obtained depend on an improvement in diet quality, a generalized linear model will be used. Sensitivity analyses will be performed on all outcomes to (1) determine if missingness of the outcome data is associated with prognostic characteristics at baseline and treatment group; (2) compare the results obtained with those following an intention-to-treat analysis where missing outcomes are handled using multiple imputation by chained equations, an analysis on a complete case per protocol, and a per-protocol analysis where missing outcomes are handled using multiple imputation by chained equations; and (3) to explore potential sources of heterogeneity in treatment effects. We thus plan to test the effect of various covariables including age, pre-pregnancy BMI, parity, gestational weight gain, GDM risk factors, fasting blood glucose in the first trimester, GDM diagnosis in the second trimester, adherence to the intervention (with a weighted model based on the level of participation in the intervention), and intervention delivery mode (in person of virtually). Those analyses will ensure a more comprehensive understanding of how different factors may influence the intervention’s outcomes in diverse subgroups of the study population. Programming codes will be tested with a dummy data set to ensure their validity. No preliminary or interim analyses are planned. An exploratory health-economic analysis could be conducted *post hoc*.

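### The HOMA-IS formula in Section 2.7.1 rises with insulin and glucose, so it measures resistance, although Section 1.5 names it a sensitivity index and its change is tested one-sided

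*Protocol article*

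**What the plan says.** Section 1.5 of the protocol article (Study objective and outcomes) lists among the secondary outcomes the "Homeostatic Model Assessment for Insulin Sensitivity (HOMA-IS) index, which estimates the hepatic insulin sensitivity". The next item there is the "Matsuda index which estimates overall insulin sensitivity (hepatic and peripheral").

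Section 2.7.1 (Glucose homeostasis outcomes) gives the formulas. HOMA-IS is "HOMA-IS [Fasting insulin (μU/ml) × fasting glucose (mmol/L)/22.5"; the Matsuda index is "10,000/[fasting glucose × fasting insulin × (mean glucose × mean insulin)]^1/2".

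Section 2.10.2 (Statistical analyses) covers "Changes from first- to third-trimester measurements of the primary and secondary outcomes between the intervention and control groups". The t-test specified for these comparisons is for two samples and one-sided ("will be assessed using a two-sample one-sided"). The section names no direction for any outcome. Section 1.4 expects the glucose homeostasis indices to improve, again without a sign for each index.

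**The concern.** An index of insulin sensitivity should fall as fasting insulin and fasting glucose rise. The printed HOMA-IS has both quantities in the numerator, so it rises with them. The Matsuda index has both in the denominator, so it falls. As printed, two secondary outcomes with the same kind of label point in opposite directions.

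With a two-sided test, a sign inversion would lead to a misworded result, but the difference could still be detected. With a one-sided test the chosen tail decides what can be concluded. The index name is the only guide to direction that the article gives for HOMA-IS. An analyst who codes the formula as printed and takes the tail from the name would be looking for an effect in the unfavourable direction.

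**Working it through.** **Plan's own figures.** The article gives no numerical value for HOMA-IS, so there is none to reproduce. The sample size is used here only to set a realistic number per arm. A one-sided two-sample t-test with effect size 0.5, alpha 0.05 and 80% power needs 51 per arm. With all the stated losses added (4% + 8% + 20% = 32%), 102/0.68 = 150, the planned total. Counting only the 20% dropout leaves 150 × 0.80 = 120, or 60 per arm. The checks below use 51 to 60 per arm.

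**Step 1: direction, from the printed formulas alone.** Let fasting insulin and fasting glucose each fall by 10%.
- Printed HOMA-IS: 0.9 × 0.9 = 0.81, a fall of 19%.
- Reciprocal, 22.5/(insulin × glucose): 1/0.81 = 1.235, a rise of 23%.
- Matsuda, with the mean OGTT values held fixed: 1/√0.81 = 1/0.9 = 1.11, a rise of 11%.

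The same metabolic improvement lowers the printed HOMA-IS and raises the Matsuda index.

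**Step 2: three illustrative profiles.** All values are assumed. The Matsuda column also uses assumed mean OGTT values, with glucose converted to mg/dL.

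| Fasting insulin (μU/ml), glucose (mmol/L) | Printed HOMA-IS | Reciprocal | Matsuda |
|---|---|---|---|
| 5, 4.4 | 22/22.5 = 0.98 | 1.02 | 8.5 |
| 10, 4.6 | 46/22.5 = 2.04 | 0.49 | 4.2 |
| 20, 5.0 | 100/22.5 = 4.44 | 0.23 | 1.9 |

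Down the table, the printed index rises while the reciprocal and the Matsuda index fall.

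**Step 3: consequence under the one-sided test, if the tail follows the name.** Take the printed index, a one-sided 5% t-test for intervention higher, and an assumed standardised difference d in the change. The rejection probability comes from the noncentral t distribution with noncentrality ±d√(n/2). For d = 0.5 this is ±2.52 at 51 per arm and ±2.74 at 60.

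| Assumed d | True benefit declared | True harm declared a benefit |
|---|---|---|
| 0.5 | below 0.0001 | 0.81 to 0.86 |
| 0.2 | 0.003 to 0.004 | 0.26 to 0.29 |

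By symmetry, the printed index tested for intervention lower would detect a true benefit of d = 0.5 with probability 0.81 to 0.86. The loss comes wholly from combining the printed formula with the tail that its name suggests.

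**The case against.** The strongest reply is that a wrong conclusion is not built into the plan. Section 2.10.2 says one-sided but fixes no direction, and Section 1.4 speaks only of improvement. The analysts must set a sign for each outcome in any case, because 2-h glucose and the glucose iAUC improve by falling while the Matsuda index improves by rising. Anyone who recognises the printed expression as a resistance index would test for lower and lose nothing. This stands, and it makes the consequence conditional.

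A reader might also infer that the HOMA and Matsuda results would contradict each other as evidence, or that every secondary comparison is exposed. Neither is supported. Opposite signs are a labelling problem, just as fasting glucose and the Matsuda index move in opposite directions without conflict. The one-sided sentence covers first-to-third-trimester changes; the first-to-second-trimester changes also listed in Section 1.5 fall outside it, although they would use the same misdefined index.

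The reciprocal may have been lost in print: an operator is also missing between the two glucose terms of the insulinogenic index in the same section. That is possible but cannot be confirmed. The exponent in the Matsuda formula survived, and the HOMA-IS expression is complete as it stands, so nothing warns a programmer.

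Finally, direction may be set in an analysis plan that is not shown. That would answer a missing detail, but here the article states a formula that conflicts with its own definition.

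**Conclusion.** The definitional error holds and can be shown from the article alone: Section 1.5 describes a sensitivity index and Section 2.7.1 prints its inverse. For 10% falls in both inputs, the two versions differ by a 19% fall against a 23% rise.

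The inferential risk is real but needs two things together: the formula coded as printed, and the alternative set to higher because of the name. Under those conditions, with assumed d = 0.5 and 51 to 60 per arm, a true benefit is practically never declared, and a true harm of that size is declared a benefit in 81% to 86% of trials. The effect sizes are assumptions; the article gives no expected effect or variability for this index.

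The scope is one secondary outcome. A reader might infer that the trial's main result is at risk. It is not: the primary outcome is fasting plasma glucose, the sample size of 150 rests on it, and the disposition index is built from the Matsuda and insulinogenic indices, so none of these uses HOMA-IS. The underlying insulin and glucose measurements are collected in any case, so the index can be recomputed. The error should be corrected before analysis, but it is of moderate weight.

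**What to change.** Choose one of two equivalent corrections:
- define HOMA-IS in Section 2.7.1 as 22.5/(fasting insulin × fasting glucose), with higher as better; or
- keep the printed expression, rename the outcome HOMA-IR in Sections 1.5 and 2.7.1, describe it as insulin resistance, and state that lower is better.

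In either case, make the two sections agree and state, before any comparison of the groups, the favourable direction of this index for the one-sided test in Section 2.10.2. Check the analysis code against the corrected definition; the dummy-data test that Section 2.10.2 already plans is a convenient place.

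The cost is a line or two of wording and a code check. Sample size, data collection and participants are unaffected. No interim analysis is planned, so the correction can be made before the groups are compared.

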#### Dietary outcomes

2.7.2

Three automated, self-administered, and validated 24-h dietary recalls (R24W) using the *Rappel de 24 heures Web* virtual platform, developed and hosted by the *Institut sur la nutrition et les aliments fonctionnels*, at *Université Laval* and validated among Canadian pregnant individuals (69–71). It will be used to measure food intake at each trimester and 3 months postpartum. The R24W platform allows the research staff to randomly select 3 days (2 weekdays and 1 weekend day) in each trimester. On the days the R24W needs to be filled, an email will be sent to the participants, asking them to record all foods and beverages they had the day before (24-h period). Individuals who do not have access to a computer, tablet, or cell phone to complete these online questionnaires (and other questionnaires detailed below) will be invited to complete them on-site, during their on-site visit or the following days at the research center, where a tablet will be provided for the time needed to complete the questionnaires. The 2018 version of the 2015 edition of the Canadian Nutrient File (72) is used to code every food item that is offered on the web platform, enabling the automatic extraction of nutritional data. If a participant fails to complete the R24W, subsequent emails will be sent, within the trimester, until three R24Ws are completed.

Diet quality will be measured using the Healthy Eating Food Index 2019 (HEFI-2019) score, using the mean intakes from repeated R24W (73). This score was recently developed and validated among Canadian adults (74). The HEFI-2019 includes 10 components, of which five are based on foods, one on beverages, and four on nutrients, with a total score of 80 points, with a higher score representing a greater level of adherence to the CFG recommendations on healthy food choices. Since the intervention is based on the 2019 Food Guide, we believe this is the best index to use.

#### Quality of life

2.7.3

Quality of life will be evaluated in the third trimester using the 36-Item Short Survey (SF-36) (75), which has been previously used among pregnant populations across the globe (76, 77). The SF-36 includes a multi-item scale that assesses eight health concepts: (1) limitations in physical activities because of health problems; (2) limitations in social activities because of physical or emotional problems; (3) limitations in usual role activities because of physical health problems; (4) body pain; (5) general mental health (psychological distress and well-being); (6) limitations in usual role activities because of emotional problems; (7) vitality (energy and fatigue); and (8) general health perceptions.

#### Acceptability and feasibility of the intervention

2.7.4

In this prospective study, we will thoroughly assess both the acceptability and feasibility of the proposed nutritional intervention. To evaluate acceptability, we will employ a mixed-methods approach. Quantitative data will be collected through a 38-item in-house questionnaire among participants receiving the intervention only. This survey aims to capture their perceptions of the intervention’s relevance and appropriateness, and to gather information on their overall satisfaction with the components of the intervention, including the individual counseling sessions, the video clips, and the virtual community, using Likert scales. A content analysis of the Facebook group could also provide qualitative insights into participant engagement and interactions within the community, assessing the depth of discussions, sharing of experiences, and support provided. Attendance to the sessions with the nutritionist will be recorded, as well as their duration. Participants will be questioned regarding their viewing of the video clips at each research visit and intervention follow-up. The engagement metrics on the virtual community include observations such as participation (i.e., if the participant have joined the Facebook group or not), as well as, the number of views, likes, and comments by participants. This multi-faceted approach provides a comprehensive view of participant adherence and engagement with each intervention component throughout the study. Feasibility will be assessed by comparing recruitment rates to predetermined targets. Reasons for non-participation will also be collected from eligible participants who declined participation. Additionally, participant retention rates will be monitored throughout the study, considering a dropout rate of less than 20% as indicative of feasibility. Barriers to participation and reasons for drop-out will also be recorded. Adherence to the intervention will be assessed using activity logs and tracking of engagement metrics within the platform on which the video clips are hosted and the virtual community. An assessment of the intervention’s compatibility with the protocol, available resources, and timeline will be conducted through continuous process evaluations. Therefore, we plan to document resource utilization (time, personnel, and financial resources required for intervention delivery) to compare these to the initially projected allocation and to assess whether the intervention was delivered within the planned time frame, identifying any delays or deviations from the study schedule. This will allow us to comprehensively assess intervention delivery, identifying challenges, successes, and opportunities for refinement with the research team and setting. The outcomes of these evaluations will be pivotal in refining the RCT design, optimizing intervention delivery, and enhancing overall study viability throughout the project.

#### Other variables

2.7.5

##### Sociodemographic status

2.7.5.1

A socio-demographic web questionnaire including questions on age, ethnicity, education, employment status, relationship status, parental status, family income, and place of residence will be completed. Recognizing that individuals who do not identify as female also have perinatal needs and experiences that may be similar to, but also different from cisgender women (78), an additional question was added to collect information on participants’ gender identity.

##### Medical history, medication, and dietary supplements used

2.7.5.2

A self-administered questionnaire will be used to evaluate the participants’ relevant medical history, use of medication, natural products, and dietary supplements.

##### Anthropometric measurements

2.7.5.3

Height and pre-pregnancy weight will be self-reported by participants at screening. Height will be confirmed at V1 by a trained research assistant using a stadiometer. Weight is measured at each research visit using a scale. Pre-pregnancy BMI [weight (kg)/height (m)^2^] will be calculated using self-reported pre-pregnancy weight and on-site measured height. GWG will be calculated using body weight values during pregnancy collected retrospectively from medical records. Total GWG will be calculated as the difference between the last measured body weight value and the self-reported pre-pregnancy weight.

##### Eating behaviors and Intuitive eating

2.7.5.4

The Dutch Eating Behaviors Questionnaire (DEBQ) will be used to measure participants’ eating behavior at every trimester and 3 months postpartum (79). This self-administered 33-item tool assesses three distinct eating behaviors in adults: (1) emotional eating; (2) external eating; and (3) restrained eating. Intuitive eating will be assessed at every trimester and 3 months postpartum using the Intuitive Eating Scale-2 (IES-2) (80, 81), used and validated in pregnancy (82). This 23-item questionnaire evaluates four subscale scores as well as a total intuitive eating score summing the four subscale scores: (1) eating for physical rather than emotional reasons; (2) unconditional permission to eat; (3) reliance on internal hunger and satiety cues; and (4) body−food choice congruence.

##### Physical activity

2.7.5.5

Physical activity behavior during every trimester will be assessed online using a self-administered French translated and validated version of the Pregnancy Physical Activity Questionnaires (PPAQ) (83, 84). The PPAQ version used in this study consists of a 33-item semiquantitative questionnaire that asks respondents to report the time spent participating in activities including household/caregiving, occupational, sports/exercise, transportation, and inactivity. At 3 months postpartum, the physical activity habits during the last 7 days will be assessed using the International Physical Activity Questionnaire (IPAQ) (85).

##### Perceived stress and anxiety during pregnancy

2.7.5.6

The Perceived Stress Scale (PSS-10) will be used to assess stress levels at every trimester and 3 months postpartum, which has been widely used in both the prenatal and postpartum periods (86). The Pregnancy-Related Anxiety Questionnaire (PRAQ-R2) will be used to specifically evaluate participants’ anxiety in their first trimester (87). This 10-item tool assesses three dimensions of pregnancy-related anxiety: (1) fears about fetal health; (2) fear of childbirth; and (3) concerns about their physical appearance.

##### Motivation

2.7.5.7

Since intrinsic motivation is a key concept of the theoretical model we use and is used as a lever to achieve the objectives of the intervention (46), it will be measured in the first and the third trimester using the Regulation of Eating Behavior Scale (REBS) (88). This scale evaluates the different behavioral regulatory styles: (1) intrinsic motivation; (2) the four types of extrinsic motivation (integrated, identified, introjected, and external regulation); and (3) motivation.

##### Social support

2.7.5.8

A self-administered two-item questionnaire will be used to measure the perceived social support received by participants on improving their eating habits in the last 6 months. The questions in this tool are designed to assess: (1) the sources of social support participants could count on to help them improve their eating habits as well as (2) their level of satisfaction with the support received.

##### Pregnancy outcomes

2.7.5.9

A self-administered questionnaire will be used in the first trimester to evaluate the participants’ obstetrical history. At every trimester, participants will also complete a questionnaire collecting information about frequent prenatal discomforts that could impact their dietary habits, such as nausea, and vomiting, as well as cravings and aversions. Other variables will also be collected in medical records at the end of the study, pregnancy complications and management, gestational age at delivery, delivery method, as well as birth outcomes (i.e., neonatal anthropometric measures, delivery complications).

##### Variables collected during follow-ups

2.7.5.10

Variables collected during the nutrition counseling sessions and phone follow-ups, such as the duration of the meeting, the type of goals (i.e., specific food groups, purchase of certain foods or frequency of restaurants, etc.), and the level of goal achievement will also be collected retrospectively from the participant research record.

### Data management and monitoring

2.8

The research measures and outcomes are recorded using online questionnaires and paper forms at specific time points. Research team members ensure the integrity of the data before entering it into the FANI centralized web-based database. The research coordinator is responsible for training research staff and health professionals (dietitians and nurses) involved in the research project, as well as monitoring activities.

The trial steering committee includes the principal investigator, two co-investigators with complementary expertise in GDM management, two external investigators with extensive experience in clinical trial methodology, a dietitian involved in health service delivery, an engaged patient-partner, the study coordinator and research team members. Their involvement began during the protocol design stage, and they meet periodically to provide guidance and to support the coordination of the study. Formal meetings will be held twice a year to review the progress of the study and any problems that may arise in the conduct of the study. The following potential issues will be discussed: recruitment, ineligibility, protocol violation, adverse effects, dropout rates, completeness and timeliness of data, and balance between study arms. The coordinator will be responsible for scheduling the trial steering committee meetings.

The data monitoring committee will include the principal investigator, two external physicians and clinical investigators with extensive experience in diabetes and pregnancy follow-ups, and the study coordinator. Formal meetings will be held to review any clinical problems that arise in the conduct of the study if needed.

